## **2.2 Rationale for current study**

Treatment of toddler's fractures via immobilisation of the leg can be associated with other complications. This includes pressure sores, skin breakdown, stiffness of the ankle and knee joint as well as pain from the cast rubbing. Use of immobilisation impacts on activities of daily life for children and their families. It also can lead to delayed recovery from the injury by limiting movement and causing temporary stiffness and weakness of the limb.

The potential advantages of a conservative approach (observation and no immobilisation) are ease of care of the child with a quicker recovery from the injury and no risk of complications from the cast or boot. Avoiding immobilisation allows free movement and prevents the need for frequent visits to check or remove the cast if

used. It prevents stiffness developing in joints that have been rigidly immobilised and potentially allows earlier return to normal activities once pain from the fracture has settled. Toddler's fractures are by definition stable injuries and tend not to displace if not immobilised. Furthermore, in cases where a toddler's fracture is the presumptive diagnosis but a bone or joint infection or minor injury is eventually diagnosed, immobilisation may delay definitive diagnosis.

However, there are concerns that without immobilisation there is a risk of the broken tibia displacing, that more pain is felt during recovery, and a risk of worsening of the injury. The inability to participate in normal activities such as attendance at nursery may also be affected. These may all impact on the child's and carer's wellbeing. Immobilisation allows the limb to be held still, relieving discomfort from the fracture associated with joint movement and maintains the ability to bear weight while the fracture heals.

Despite toddler's fractures being common injuries, there is no universally accepted way to treat these fractures with great variability in management across the UK and the rest of the world due to a lack of well conducted trials. The use of a cast may be an unnecessary treatment that causes discomfort, delayed recovery and unnecessary cost to healthcare organisations. There is therefore a requirement for a large-scale, high-quality randomised controlled trial comparing immobilisation vs no immobilisation.

A recent example of a paediatric orthopaedic randomised and controlled equivalence trial, the FORCE trial, compared immobilisation in a removable splint to a bandage for torus fractures of the radius. There are some parallels with toddler's fractures in that both injuries heal quickly without long term problems, but inferring treatments from this study is difficult for a few reasons. Firstly, the tibia is a weight bearing bone and causes functional issues as well as pain. Secondly, use of a bandage in the upper limb is straightforward, but in the lower limb these slip off very easily and their use is therefore not standard. FORCE does however show that the planned treatment arms will be suitable for the trial.

As part of the preliminary work for this study, parents who had a toddler who previously underwent treatment at Sheffield Children's Hospital were contacted to take part in an online survey. The majority of these toddlers were treated with a cast. The survey asked if they would consider a study to allocate their child to treatment with or without a cast assuming both are considered equal. Of 14 responses, 12 responded 'yes'.

Other information was gathered on expected difficulties in both arms, the length of follow-up, and how they would like to receive information. This information was used to develop the study protocol and associated documents.

The study will be conducted in accordance with the protocol and International Conference on Harmonisation Good Clinical Practice (ICH-GCP).

### **3. Aims and objectives**

#### **3.1 Aims**

- To discover whether no immobilisation is non-inferior to immobilisation in regard to pain at 7 days post randomisation, in children aged from 9 months up to and no later than their 4th birthday, who present with clinically suspected or diagnosed toddler's fractures.
- To explore whether no immobilisation has an impact on satisfaction with treatment, complications, and recovery time compared to immobilisation.

#### **3.2 Objectives**

1. To determine whether no immobilisation is non-inferior to management by immobilisation in this population in relation to pain by undertaking a multicentre RCT.
2. To determine patients' and parent/guardians' experience, recovery and satisfaction with the two treatments.
3. To evaluate the relative cost-effectiveness of no immobilisation compared to immobilisation by undertaking a within-trial economic evaluation from both an NHS and a societal perspective.

### **4. Trial Design**

A multicentre, prospective, parallel group, individually randomised (1:1), pragmatic, non-blinded controlled non-inferiority trial with 4 week follow up and within-trial health economic analysis.

The trial aims to recruit 494 participants and will be conducted in approximately 20 NHS Trusts, including specialist Children's Hospitals; Tertiary units that treat children and District General Hospitals. Participants will be primarily recruited in Emergency

Departments, and in Fracture clinics if required. Eligibility will be confirmed by the researcher and study information given. Parents/guardians will be given time to consider the interventions following receipt of information about the study. Written consent will be taken from parents/guardians after any questions have been addressed. Due to the young age of participants, assent will not be obtained. Participants whose parents/guardians have consented will be randomised to receive either immobilisation, or no immobilisation, then followed up for 28 days.

A 6-month internal pilot, with clear progression criteria to full trial (see section 8.3) will follow the recommendations of Avery et al, and assess the feasibility of site set-up and recruitment.

The internal pilot trial will use data from all sites which are open to recruitment within the first 6 months after the first site is opened. To allow time for collation of site and participant recruitment, and primary outcome, the progression criteria will be assessed by the Trial Steering Committee at the end of the following month. Data from the internal pilot will be included in the final analysis. At the end of the internal pilot phase, if any amber criteria are met, a recovery plan detailing remedial actions will be agreed with the Trial Steering Committee and submitted to the funder.

#### **4.1 Blinding**

Blinding of participants, or their parents/guardians (who complete the primary outcome assessment), or those delivering the intervention is not possible. The trial statistician(s) will remain blinded at least until the statistical analysis plan has been signed off and approved by the oversight committees. They may be unblinded thereafter to prepare for the final analysis.

## 5. Selection of participants

[figure not shown]

## **5.1 Inclusion criteria**

Inclusion Criteria:

1. Children aged from 9 months to their 4th birthday at time of initial presentation to hospital
2. Clinically suspected or confirmed toddler's fracture of the tibia as determined by standard guidelines at the recruiting site.

## **5.2 Exclusion criteria**

1. Suspected non-accidental injury requiring further imaging or investigation
2. Associated displaced fibula fracture
3. Comminuted/complex fracture patterns of the tibia
4. Physeal injuries of the tibia
5. Multiple fractures
6. Metabolic bone disease
7. Congenital anomalies involving the lower limb and foot (limb deficiencies)
8. Has previously participated in the ToTs Study

## **5.3 Participant identification**

Sites should make every effort to recruit patients with suspected or confirmed toddler's fractures at their first attendance to emergency department (ED). Patients can also be identified at fracture clinics if necessary. Appropriately trained and delegated site staff will discuss the study with the parent/guardian, ideally in person, but with the option of phone/videocall if necessary, and provide access to the parent/guardian information materials. This includes a short recruitment animation, and a parent/guardian information sheet. Translations will be available in six languages other than English, which will be based on the 2021 Census, and information from recruiting sites on the common languages in their local authority areas.

## **5.4 Informed consent process**

Eligibility will be confirmed by appropriately trained clinicians listed on the delegation log, and overall responsibility for eligibility assessment sits with the site PI. Interpreters will be available through standard NHS processes for the consent process, as required.

Informed consent will be taken from the parent/guardian (who has parental responsibility) by a trained and delegated member of the study team. This will ideally take place as soon as possible after identification, in person, during their ED attendance.

If patients are initially sent home from ED as part of routine care (before they are recruited to the study), but then the patient and parent/guardian present at a fracture clinic, consent may be obtained at the fracture clinic instead of at ED. Consent (and randomisation) can take place remotely if required, or requested by the parent/guardian, but the parent/guardian must be willing to return for their child's treatment if randomised to receive it.

Before consent, participants will have been provided with the patient information materials and will have had time to consider their potential participation. They will have the opportunity to ask any questions, before providing consent. They can take away the information to consider, if they request to do so. Parent/guardian consent must be obtained for the patient to be able to take part in the trial.

## **5.5 Co-enrolment guidelines**

Co-enrolment in other interventional studies is not permitted during participation in ToTs. Consideration should be given to potential data collection burden associated with other concurrent studies, such as observational studies.

## **6. Randomisation and enrolment**

Prior to randomisation, baseline data will be collected, including patients' post code, contact details, ethnicity and sex. Parents/guardians will complete the FLACC to provide a baseline measure.

Randomisation should take place as soon as possible after initial presentation at the ED or fracture clinic, and no later than three days after initial presentation. Ideally this will take place whilst the patient is still in the ED, but can be done in fracture clinic, or remotely, if necessary.

Once eligibility is confirmed, parent/guardian consent and baseline assessments are obtained, participants will be randomised 1:1, using an online system provided by the Sheffield CTRU, to no immobilisation or immobilisation, using minimisation with a random element and the following factors ensuring baseline balance: site, age ( $\leq 2$  years vs.  $> 2$  years) and radiologically confirmed fracture (yes vs. no).

The initial participants will be allocated to their treatment using simple randomisation to seed the minimisation algorithm.

Patient details (Identification number, date of birth and stratification information) will be entered into the randomisation system and the treatment allocation will be returned. Randomisation will be done by site staff. Patients and their parents/guardians will be informed of their trial allocation in person (or via phone/video call if randomised remotely), and this will also be documented in the medical records. Their General Practitioner (GP) will also be informed of their participation in the trial, and their treatment allocation. Randomisation is Day 0 in regards to study follow-ups.

## **7. Trial treatment**

### **7.1 Patients randomised to 'Immobilisation'**

Participants should receive an above knee or below knee cast, or control action motion boot as per standard local practice. These should be applied in the ED, plaster room or fracture clinic by appropriately trained staff. If a cast, the type used will depend on local policy and preference of the treating clinician, as a Plaster of Paris backslab or full cast, a synthetic soft cast, or a synthetic full cast. Casts will include an underlayer of wool with optional use of stockinette and adhesive felt for pressure areas. Temporary backslabs may be used initially. The type of material used will be pragmatic and depend on the acute hospital standard care for cast application.

Treatment should be given as soon as possible after randomisation, and within three days of initial presentation (by the end of the third day) at the latest. Immobilisation should continue for at least 7 days after fitting, and ideally a minimum of 2 weeks after it is given. If participants were already in immobilisation prior to randomisation, the same immobilisation can remain on, if suitable.

Where a temporary backslab was applied, change to a definitive immobilisation will be documented. On occasion, as part of standard care, a change of definitive immobilisation may be required if for example a cast becomes soft or damaged, or if complications such as pressure sores arise. All changes will be collected.

Parents/guardians will be given written information about duration of wear, and removal of the immobilisation, as per site standard protocols. Sites will provide care advice sheets as per their standard protocol. Participants will be followed up in ED/ fracture clinics as per the local site normal treatment pathways. Advice as to analgesia will follow local routine care pathways.

Removal of immobilisation by parents/guardians will be recorded either in medical records or as part of questionnaires sent to parents/guardians, to allow for assessment of the fidelity of the intervention.

## **7.2 Patients randomised to 'No Immobilisation'**

If participants have received immobilisation prior to randomisation, this must be removed within 3 days of initial presentation to the Emergency Department (by the end of the third day) at the latest, and as soon as possible after randomisation. Participants should not receive any immobilisation after randomisation for at least 7 days (until the end of the 7th day), but ideally not at all.

Participants can be offered a soft bandage at the discretion of the site/clinician. It is a personal choice if participants/parents/guardians would like to accept this or not. Parents/guardians may be given written information about duration of wear, application and removal of the bandage, as per site standard protocols.

Participants will be followed up as per usual treatment pathways at the local site. Advice on analgesic use will follow routine local care pathways.

## **7.3 Treatment adherence**

Treatment change will be discouraged. Sites will discuss with parents/guardians the importance for the trial of remaining in their allocated treatment and will establish equipoise before the patient is randomised. However, if a parent/guardian still does wish to change their child's treatment after randomisation they can do so.

For participants randomised to the immobilisation arm, non-adherence is defined as follows:

- Removing the immobilisation prior to the 7th day after fitting (inclusive, i.e., up until the end of the 7th day),
- Not receiving any immobilisation by day 3 after initial presentation

For participants randomised to the non immobilisation arm, non-adherence is defined as follows:

- Receiving any new immobilisation before the 7th day after randomisation (inclusive, i.e. up until the end of the 7th day).
- Not removing any immobilisation fitted prior to randomisation by day 3 after initial presentation

Information on all immobilisation received during the will be recorded, including fitting/removal dates (from medical records/parent questionnaires), and the reason for change where available.

## **8. Outcomes**

### **8.1 Primary outcome/endpoint**

The primary outcome is pain measured at 7 days post randomisation. This will be assessed by the FLACC (Face, Legs, Activity, Cry, Consolability) behavioural pain assessment scale. The revised FLACC will be used for children with cognitive impairment.

Seven days was selected as our primary outcome based on our retrospective review of Toddler's fractures at Sheffield Children's Hospital, our PPIE work and survey of clinicians. This time point is identified as the most important for assessment as acute pain in the vast majority of children would have resolved and is the key point at which differences in treatment will be identified if taking baseline into consideration. PPIE consultation confirmed the use of this validated outcome measure with reporting via proxy would not overburden families.

## 8.2 Secondary outcomes/endpoints

Collected via medical note review by site staff at 28 days post randomisation:

- Planned and unplanned attendances to ED, plaster room, or fracture clinics
- Use of plain radiograph imaging on the affected limb since randomisation.
- Occurrence of and treatment for pressure ulcers, resulting from the use of immobilisation.
- Occurrence of and treatment for fracture displacement.

Collected via parent/guardian questionnaires:

- Pain (via FLACC scale or Revised FLACC) at 3 days and 28 days post randomisation.
- Recovery of mobility (time to weight bear) (asked at 3 days, 7 days and 28 days post randomisation if mobility was not recovered by previous timepoint).
- Requirement for and type of oral analgesia up to day 7 (asked at 3 days and 7 days).
- Resource use and contact with GPs since randomisation (asked at 28 days post randomisation).
- Satisfaction with allocated treatment assessed by Likert Scale and open question (asked at 28 days post randomisation).
- Removal of immobilisation (asked at 3 days, 7 days and 28 days)

These timepoints are based on the minimal risk of long-term problems with these injuries and associated pain not persisting beyond 4 weeks due to healing.

### 8.3 Internal pilot outcomes

A 6-month internal pilot to assess feasibility of site set-up and recruitment (Table 1).

**Table 1:** Internal Pilot progression criteria

|                                                                                       | Red: Consider ending study if at least TWO criteria are met. | Amber: Proceed with protocol amendments and remediation, as agreed with TSC | Green: Proceed |
|---------------------------------------------------------------------------------------|---------------------------------------------------------------------|------------------------------------------------------------------------------------|-----------------------|
| No. of sites open and recruited 1st participant                                       | <60% (n<12)                                                         | $\geq 60\%$ (n=12-19)                                                              | 100% (n=20)           |
| No. of participants recruited                                                         | <60% (n<60)                                                         | $\geq 60\%$ (n=60-99)                                                              | 100% (n=100)          |
| Mean recruitment rate per site                                                        | <50% (<0.8)                                                         | 50-99% (0.8-1.62)                                                                  | 100% (1.63)           |
| Proportion of participants completed primary outcome measure of those who reached it* | <85%                                                                | 85-99%                                                                             | 100%                  |
| Adherence to allocated treatment**                                                    | <80%                                                                | 80-99%                                                                             | 100%                  |

\*The number of participants for whom primary outcome data are expected allows for time for follow-up visits to be reached, as well as for reminders to be sent and data to be processed, including return of paper questionnaires. Therefore, this data will only be included for participants who were randomised 10 days prior (if via text) or 40 days prior (if via paper) to the date that the data is extracted for the analysis.

\*\*Adherence is defined as per section 7. This information will only be available when the 28 day medical note reviews are completed. This will therefore be calculated using data from participants for whom the 28-day medical note review has been completed at the time of assessing the pilot criteria.

## **9. Assessments and procedures**

The parent/guardians will be asked to complete the FLACC pain scale, either on paper or electronically, prior to randomisation.

During the trial follow-up, parents/guardians will be given a questionnaire to complete at 3 days, 7 days, and 28 days after randomisation. In most cases, this will be sent automatically via text, as an online link to the study database. If parents/guardians indicate that they would prefer to complete this on paper, the site staff will provide all questionnaires to the parent/guardian at point of randomisation, as well as a free-post return envelope to post these back to CTRU after all are completed. Questionnaires may also be collected over the phone if necessary, if questionnaires are not completed by the primary method. Parents/guardians will be encouraged to use the same parent/guardian completing the questionnaires at all timepoints. The importance of completing the questionnaires, in particular the FLACC questionnaire, will be discussed with the parent/guardian before they consent to take part. Up to two SMS reminders will be used to facilitate completion, plus a phone call reminder for the day 7 questionnaire, or paper questionnaires, if required. Questionnaires have been designed to be as simple as possible to decrease burden on the parent/guardian and increase response rate.

The FLACC pain scale will be asked at all timepoints. Other data will be gathered by bespoke questionnaires. At 3 days, and at 7 days post randomisation, parents/guardians will also be asked about analgesia use, recovery of mobility, and removal of immobilisation (if allocated to immobilisation). At 28 days post randomisation, parents/guardians will be asked about recovery of mobility (if not recovered by day 7), satisfaction with allocated treatment, and resource use.

Responses to questionnaires will not be monitored by hospital staff, or by CTRU staff, due to the short duration of study, and to avoid impacting usual care. Parents/guardians will be informed that these data will not be monitored, and will be told to contact their medical team if they have any concerns about their child. This will also be clear in the consent form and PIS.

The FLACC scale (or revised FLACC for children with cognitive impairment) will be used in accordance with the standard guidance. Each of the five categories of the FLACC scale (Face, Legs, Activity, Cry, Consolability) is scored from 0-2, which results

in a total score between zero and ten. The scores indicate: 0 = Relaxed and comfortable; 1-3 = Mild discomfort; 4-6 = Moderate pain; 7-10 = Severe discomfort/pain. The FLACC pain scale was developed to assess post-operative pain in children, and has been validated for the assessment of pain more generally, such as post trauma. The revised FLACC (rFLACC) adds descriptors specific to the pain assessment of children with cognitive impairment, to ensure reliable pain assessments for this group of children. We are using a combination of both scores, as appropriate to the characteristics of the toddler to ensure robust, unbiased data collection, and the best possible assessment of pain.

The FLACC has been used in a number of randomised controlled trials, and our PPIE group, clinical and methodological experts believe it to be the most appropriate primary outcome measure for this trial. Pain was chosen by our Patient and Public Involvement and Engagement (PPIE) group and clinicians as the most relevant outcome. The FLACC is one of two pain scores validated for this age group. This is validated for parental administration for children with cognitive impairment. It is also commonly used to assess post surgery pain, and has been used for parental assessment of pain in research, which has shown good reliability compared to medical staff administration. Our PPIE work showed that the format of the FLACC was easy for parents to understand and that measuring on 4 occasions was not a burden due to the ease of completion and the remote access that can be used if not aligning with standard clinical care.

Medical records will be reviewed by the site team after 28 days to identify any planned/unplanned healthcare attendances, use of plain radiograph imaging after randomisation, or complications within 28 days. Data collected from medical records is routine data and no clinician training is required.

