## **9.6 Loss to contact**

Efforts will be made to contact parents/guardians, and questionnaires will be sent, for all follow-up timepoints, regardless of whether the parent/guardian has completed questionnaires at the previous time point. Two text message reminders will be sent per questionnaire time-point (at one and two days after the initial questionnaire is sent), plus a phone call reminder for the day 7 questionnaire, or paper questionnaires, if required. Questionnaires will be open for completion until the end of the trial. Date of completion will be collected and considered for the analysis. Questionnaires will close two weeks after the 28 day follow-up timepoint for the last recruited participant.

After the study closes, participants will be defined as lost to contact if no questionnaire data is available for one follow-up time point, and all subsequent stipulated follow-up time points.

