### **11. Statistics**

#### **11.1 Sample size**

The sample size of 494 (247 per arm) was based on a non-inferiority margin of one point on the FLACC, an expected conservative standard deviation of 3.3, with a one-sided alpha of 0.025, and 90% power, 15% loss to follow-up and a conservative estimate of correlation with baseline FLACC values of 0.3.

The non-inferiority margin was chosen based on face-to-face meetings with parents of children who had previously sustained a toddler's fracture. Pain levels in general and the FLACC scale in particular were discussed. Parents were asked to identify what difference in score they felt would reflect a difference in treatments for toddler's fractures. There was universal agreement that they would consider alternatives to

immobilisation management for their toddler's fractures only if this did not increase pain by more than one point in the FLACC score.

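### Families using paper return the day-7 primary FLACC only after day 28, and no day or trigger is set for the phone call that could rescue it

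*Protocol*

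**What the plan says.** Section 9 makes a text link the usual route for the day-3, day-7 and day-28 questionnaires. Families who prefer paper are handed all the forms at randomisation, "as well as a free-post return envelope to post these back to CTRU after all are completed".

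The pilot footnote in section 8.3 reflects the delay. Primary outcome data count as expected once a participant was randomised 10 days earlier by text, but "40 days prior (if via paper".

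The safeguards are in sections 9 and 9.6:
- two text reminders per time point, one and two days after the questionnaire is sent;
- "plus a phone call reminder for the day 7 questionnaire, or paper questionnaires, if required";
- collection by phone where the form was not completed by the main route.

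Section 9.6 keeps questionnaires open until the end of the trial and records the completion date for consideration in the analysis. Baseline FLACC is completed before randomisation (section 6) and is not part of the posted set.

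Section 11.1 plans for "with a one-sided alpha of 0.025, and 90% power, 15% loss to follow-up".

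**The concern.** The phone reminder and phone collection both depend on someone knowing, around day 7, that the score is missing. For text families the database shows this at once. For paper families nothing comes back until the whole set is posted, three weeks after the primary time point. The text-reminder clock does not obviously help either, because it starts when a questionnaire is sent and the paper forms are handed over on day 0.

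FLACC scores observed behaviour, so a day-7 score cannot be observed later. Section 8.2 expects pain not to persist beyond four weeks, so a score taken after day 28 says little about day 7.

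The single envelope adds a second weakness. The model in section 11.2 takes the day-3, day-7 and day-28 scores as outcomes. A child who misses only day 7 still contributes through the other two visits. A child whose envelope never arrives has no outcome at all and adds nothing to the day-7 comparison. A day-7 form completed on time is therefore lost if the family drops away before posting.

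**Working it through.** **1. What is visible, and when**

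| | Text | Paper |
|---|---|---|
| Day-7 form reaches CTRU | on completion | with the day-28 form |
| Pilot allowance after randomisation (8.3) | 10 days | 40 days |
| Text reminders (9.6) | 1 and 2 days after sending | no sending date after day 0 |
| Phone reminder (9, 9.6) | day-7 questionnaire, conditional | paper questionnaires, conditional, no day given |
| Phone collection (9) | if not completed | if not completed, but returns cannot show this before day 28 |

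**2. Reproducing the planned size**

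Inputs from section 11.1: margin 1 point, SD 3.3, one-sided alpha 0.025, power 90%, baseline correlation 0.3, loss 15%. True difference is taken as 0.

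- Adjusted SD = 3.3 × √(1 − 0.3²) = 3.148, so variance = 9.910.
- n per arm = 2 × (1.960 + 1.282)² × 9.910 = 208.3, rounded up to 209.
- With 15% loss: 209 / 0.85 = 245.9, so 246 per arm and 492 in total.

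The protocol states 494 (247 per arm). The figure reproduces to within two participants.

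**3. Overall loss**

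The protocol does not give the paper share s or the paper non-return rate q. Assumptions: s = 10–30%, q = 20–40%, and 15% loss among text families.

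Overall loss L = s × q + (1 − s) × 0.15

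- Low corner: 0.10 × 0.20 + 0.90 × 0.15 = 15.5%
- Middle: 0.20 × 0.30 + 0.80 × 0.15 = 18.0%
- High corner: 0.30 × 0.40 + 0.70 × 0.15 = 22.5%

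The excess over plan is 0.5 to 7.5 percentage points, or 494 × 0.005 = 2.5 to 494 × 0.075 = 37 participants.

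**4. Power**

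With m = 247 × (1 − L) analysed per arm, power = Φ(√(m/2) / 3.148 − 1.960).

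| Overall loss | m per arm | Power |
|---|---|---|
| 15% | 210.0 | 90.2% |
| 15.5% | 208.7 | 90.1% |
| 18% | 202.5 | 89.2% |
| 20% | 197.6 | 88.4% |
| 22.5% | 191.4 | 87.4% |
| 25% | 185.3 | 86.4% |

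Even the high corner costs under 3 points of power.

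**The case against.** The strongest reply is that the protocol already names paper questionnaires in its phone-reminder provision, permits collection by phone, and takes contact details before randomisation. Nothing makes the call wait for the envelope: a call near day 7 could ask whether the form is done and take the score. This stands. A reader might infer that a missing paper score cannot be detected in time; the text does not support that. What is missing is a fixed day or trigger for the call. Scheduling could sit in an operational plan, but the condition and the posting rule are written in the protocol and are best corrected there.

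Four further points limit the concern.
- A form completed on day 7 and posted late is still a valid day-7 observation, and recording the completion date lets late entries be identified. The 40 days is an allowance for return, not evidence of loss.
- A reader might infer that a lost envelope removes every FLACC score. It removes the three post-randomisation scores only: baseline is held separately, and a current day-28 score might still be obtained by phone.
- A reader might set gross paper loss, 494 × 0.10 × 0.20 = 10 to 494 × 0.30 × 0.40 = 59 scores (2–12% of 494), against the 15% allowance. That overstates the effect, because the allowance already covers paper families. Only the excess counts.
- Bias between arms is not shown. The protocol does not describe how paper families differ or suggest that loss would differ by arm. Sensitivity analyses for missing data, including missing not at random, are planned (section 11.2).

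The pilot also monitors primary outcome completion, with below 85% as red. The criterion is not stated to be split by route, so a weakness confined to paper could be diluted in it.

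**Conclusion.** The point holds in a limited form. For paper families, the posting rule hides a missing day-7 primary score until after day 28, and the permitted phone contact has no day or trigger that would close the gap. One unreturned envelope removes all post-randomisation questionnaire scores.

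The statistical cost is modest: overall loss of 15.5–22.5% against 15% planned, and power of 90.1% down to 87.4% against 90.2%. These figures rest on an assumed paper share (10–30%), assumed paper non-return (20–40%) and 15% loss among text families, none of which the protocol states for these groups. Section 9 expects text in most cases, so paper should be a minority. The main harm is not power but a primary score that is lost or mistimed when it could cheaply have been secured. The planned sample size is not in question.

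**What to change.** In sections 9 and 9.6:

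1. Give paper families two free-post envelopes. The day-3 and day-7 forms go back together as soon as the day-7 form is complete; the day-28 form goes back separately.
2. Schedule the already permitted phone call at day 7 for every paper family, rather than leaving it conditional. The call confirms that the form is complete or takes the FLACC there and then.

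The scheduled call alone closes most of the timing gap; the second envelope removes the single point of failure. The cost is one extra pre-paid envelope and some call time for the paper minority. Sample size, treatment and analysis are unchanged. The pilot footnote's 40-day lag for paper should be reviewed to match the earlier return.
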